### Data Collection

The following items of data are recorded to allow reporting of *health services costs*:

• Number of visits to GP in last 12 months. It was decided not to record length of consultation, but to use average length from other research in calculations.

• Number of visits to practice nurse. As length of practice nurse consultations vary, an average consultation length will be estimated by research nurses during quality control visits.

• Use of hospital services: (1) Number of attendances to outpatients in last year; (2) Number of days spent as inpatient in hospital in last year; (3) Total number of days spent in hospital in last year; (4) Number of attendances to A&E in last year.

• Current prescription of medications: type and dose, using Defined Daily Dose methodology.

• The study is not in a position to record patients' use of community services, such as physiotherapy or occupational therapy.

The following items of data are recorded to allow reporting of *patient costs*:

• Occupation data.

• Travel distance, length, mode and waiting time for visits to the practice and the hospital.

• In the Republic of Ireland, GMS status.

• Patient-estimated additional expenditure or savings made in the process of lifestyle change as a result of the intervention, e.g. changes to shopping bill with changed diet, paying for exercise facilities, giving up smoking.

The following items of data are recorded to allow reporting of *capital costs*:

• Any new equipment purchased by/for the practice to carry out the intervention.

The following items of data are recorded to allow reporting of *intervention costs*:

• All expenses associated with the intervention, such as cost of training, information and education materials.

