### Level 2: Tailored patient care plans

#### (1) Initial target setting consultations

The first patient intervention consultation with the GP/practice nurse takes place as soon as possible after baseline data collection, once training of practice staff has been completed. BP and BMI are measured, diet, smoking and exercise habits reviewed and the result of the baseline cholesterol assay discussed. The patient and practitioner together identify areas of management which could be improved and the patient is invited to prioritise one particular aspect of their lifestyle for change. Possible ways of achieving targets reflecting optimal management (BP <140/90 mmHg, cholesterol <5 mmol/l, BMI <25, non-smoking, taking exercise for 30 minutes 5 days per week, eating fruit/vegetables daily and avoiding saturated fat intake, avoidance of stress) are identified. Plans for action are recorded on a personal care plan tailored for each patient and retained in the practice. The GP may also see the patient at this visit or at a further appointment within 2 weeks to determine if any change in medication is appropriate. A further follow up telephone call is made by the practice nurse to give support and address any questions 2 weeks later.

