#### (3) Regular consultations with patients for two years

Patients are invited to attend for an appointment with the GP/nurse every 4 months. At each visit a review of factors relating to targets and goals for optimal secondary prevention are made as appropriate. Goals relating to diet, smoking and exercise habits are routinely reviewed. Cholesterol is checked if it has been found to be raised at baseline, but if normal at baseline cholesterol is checked annually. Relevant measurements taken at each review visit are recorded and held in the practice and reviewed with the patient at subsequent review visits. Care which would be given according to current clinical guidelines will also be provided, as required.

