## Control Practices

Data are collected for patients in intervention and control practices in identical ways. In control practices, data are collected at baseline, one and two years post baseline. Otherwise, patients in control practices continue to receive health care as usual and the nature of this in each participating practice will be clearly described.

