## Economic Evaluation

### Introduction

The economic analysis incorporates both cost minimization analysis and cost effectiveness analysis for the various interventions for the two groups. The basic tasks of the evaluation are to identify, measure, value and compare the costs and outcomes of the alternatives being considered. Costs are likely to fall on patients, their families and the state. The health care resources consumed will reflect the costs of organising and operating the two programmes: intervention and control. These costs will reflect the time input of health professionals and fixed or overhead costs, including any new equipment and capital expenditure. All contacts with the health services are recorded and valued, including general practice contacts, hospital attendances, admissions and drug prescriptions. The patient and family costs include any out-of-pocket expenses and any own time input into the treatment process. Estimates will be made of work and leisure time foregone as part of the treatment alternatives, together with quality of life estimates. Cost-effectiveness analysis is the primary method of economic evaluation with measures of effectiveness taken from the range of primary and secondary outcomes being considered for the two groups.

In the Republic of Ireland, free healthcare is available to patients who qualify under the means-tested General Medical Scheme (GMS), although chronic disease management is not fully supported by this system. Non-GMS patients are required to pay for all of their own healthcare costs. In order that the findings of the SPHERE study will be translatable into practice within the existing healthcare systems, non-GMS patients in the Republic of Ireland will be required to pay for SPHERE-related visits to their general practice as normal. The cost of extra visits by GMS patients will be borne by the practices. The research team acknowledges that this may have an impact on recruitment of both practices and patients, although in a similar study the impact on patient recruitment was not substantial [28].

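### GP consultation length is taken from outside research and not recorded, so any extra length of GP-delivered SPHERE visits goes uncosted and the incremental cost may be understated

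*Protocol article*

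**What the plan says.** The Data Collection section under Economic Evaluation lists the items behind health service costs. The GP item is a count, "Number of visits to GP in last 12 months", followed by the valuation rule: "It was decided not to record length of consultation, but to use average length from other research in calculations". The next item treats nurses differently: "As length of practice nurse consultations vary, an average consultation length will be estimated by research nurses during quality control visits".

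GPs can deliver the intervention. The initial target-setting consultation is with the GP or the practice nurse. It covers measurements, a review of lifestyle habits, discussion of the cholesterol result, agreement on a priority for change and a written care plan. In addition, "The GP may also see the patient at this visit or at a further appointment within 2 weeks" to consider medication. For the reviews, "Patients are invited to attend for an appointment with the GP/nurse every 4 months".

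The introduction to the economic evaluation sets the costing principle for the two programmes: "These costs will reflect the time input of health professionals and fixed or overhead costs, including any new equipment and capital expenditure". Its Aim section makes the incremental comparison of costs and effects the target, and provides for reporting cost differences alone where effects do not differ significantly.

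**The concern.** An average GP consultation length from other research normally describes ordinary visits. A GP-delivered SPHERE visit is a structured consultation with several set tasks, and control patients have no such visits. If it takes longer than the outside average, the extra minutes are a real cost of the programme that the planned calculation does not contain.

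The protocol accepts this reasoning for nurses, whose consultation length is to be estimated in the trial because it varies. It gives no reason why GP consultations in the same programme should be exempt, and its own principle is that costs reflect professional time.

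At stake is the numerator of the incremental cost-effectiveness ratio or, where effects do not differ, the cost difference that is itself the economic result. Because length is not recorded, the missing minutes cannot be recovered at the analysis stage.

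**Working it through.** The protocol gives no consultation length, unit cost or cost difference, so there is no figure to reproduce. The check is algebraic, followed by an illustration.

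**What the planned rule leaves out.** Per patient over two years, let R_I and R_C be routine GP visits in the intervention and control arms, S the SPHERE visits delivered by a GP (intervention arm only), A the outside average length, and L the true mean length of a GP-delivered SPHERE visit. Suppose A is right for routine visits in both arms and is applied to all GP visits.

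- Planned incremental GP time: A × (R_I + S − R_C)
- True incremental GP time: A × (R_I − R_C) + L × S
- True minus planned: S × (L − A)

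The extra GP visits are counted; only their extra length is lost. The omitted term belongs to the intervention arm alone. It is positive if L exceeds A, zero if L equals A or no GP delivers SPHERE visits, and negative if L is below A.

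**Inputs for the illustration.**

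- SPHERE visits per patient: 1 initial visit plus 24 ÷ 4 = 6 reviews, so 7 (Intervention, Level 2). This assumes full attendance, whereas patients are only invited.
- GP share of these visits: not given. The Qualitative Evaluation section says that nurses usually run the clinics, so a low share is reasonable; 25% is assumed.
- Extra minutes, L − A: not given; 5 to 15 is assumed.
- Intervention patients: 3 centres × 8 practices × 20 patients = 480 (Sample Size Calculation).

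**Result.**

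- Lower: 7 × 0.25 × 5 = 8.75, about 9 GP minutes per patient over two years.
- Upper: 7 × 0.25 × 15 = 26.25, about 26 GP minutes per patient.
- Across 480 patients: 480 × 8.75 ÷ 60 = 70 GP hours, to 480 × 26.25 ÷ 60 = 210 GP hours.

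The result scales in proportion to the GP share, the extra minutes and attendance. A separate GP medication appointment soon after the first visit is not in the count of 7.

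**Whether another part of the plan fills the gap.** The intervention cost line is broad, but its examples are training and materials, and it cannot supply minutes that nobody recorded. No other section provides a GP consultation length measured in the trial.

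**The case against.** The strongest case on the other side is that this is an openly stated, pragmatic simplification and not a mistake. Visit counts multiplied by an outside average are a simple way to cost GP contacts, the additional visits are captured, and a condensed article may leave sensitivity analyses to a fuller plan. That stands in part: the absence of a sensitivity analysis from the article is no fault in itself. But the article does fix the decision not to record GP length, and a later analysis plan cannot undo that.

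Four stronger readings may tempt a reader, and the documents do not support them.

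- **That the result is certainly biased.** No duration is given for any consultation. Longer GP visits are inferred from the content of the initial consultation, which a nurse may carry out instead. The GP's specific added role, the medication decision, is optional.
- **That one average is prescribed for both arms and all visit types.** The rule draws no distinction, but neither does it say this in words, and it does not exclude a published length for structured reviews. The statement under Control Practices, "Data are collected for patients in intervention and control practices in identical ways", concerns how data are gathered, not how visits are valued.
- **That nurse visits are miscosted too.** Their length is estimated within the trial, and the timed consultations may well be SPHERE visits. SPHERE visits are also listed as a separate process measure under Randomised controlled trial analysis, so they can be valued separately.
- **That GPs deliver all seven visits.** This would give 7 × 5 = 35 to 7 × 15 = 105 minutes per patient, but it conflicts with the protocol's remark that nurses usually run the clinics.

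Length also does not drive every cost. In the Republic of Ireland, patients outside the General Medical Scheme pay for their SPHERE-related visits as they normally would, so the charge they bear need not depend on minutes.

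**Conclusion.** The point holds in a narrow form. Where a GP delivers a SPHERE target-setting or review visit, any time beyond the outside average is left uncosted. That time falls only on the intervention arm, so the incremental cost may be understated in the intervention's favour.

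The direction depends on SPHERE GP visits being longer than the outside average, which their content makes plausible but which no figure in the protocol shows. The size is unknown and probably modest: about 9 to 26 GP minutes per patient over two years under full attendance, an assumed 25% GP share and an assumed 5 to 15 extra minutes. Without unit costs, this cannot be turned into an effect on the cost-effectiveness ratio. The issue is confined to the economic evaluation; randomisation, power and clinical outcomes are untouched. It is a worthwhile improvement, not a serious defect.

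**What to change.** At the quality control visits already planned, where "an average consultation length will be estimated by research nurses during quality control visits", also time a sample of GP-delivered SPHERE consultations. Apply that length to the GP-delivered SPHERE visits only, and keep the outside average for routine GP visits in both arms. SPHERE visits are already counted as a process measure; the count needs to show whether a GP or a nurse conducted each one, which the article does not state. Vary the SPHERE GP length over a stated range in a sensitivity analysis of the incremental cost. If timing GP consultations is not feasible, do the sensitivity analysis alone and report that the length was assumed.

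The cost is a few extra timings at visits that will take place anyway. The intervention may look slightly more expensive as a result.

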**Figure 1 F1:**
[figure not shown]
Flow of Practices and Patients Throughout Trial.

Sample size calculations are based on the following:

• Power of 80% and alpha of 5%.

• Only patients agreeing to participate in the study and completing baseline data collection will be entered into the study. There will, therefore, be 100% uptake at the start of the study. Reasons for non-participation will be documented and recorded, and participation rates will provide a measure of the acceptability of this type of intervention to patients.

• A final completion rate of 70% is anticipated based on similar studies in the West of Ireland 7 (completion rate = 68.7%) and Dublin [28] (completion rate = 93%).

• Practice attrition of 12.5% has been allowed for (though practice attrition in another similar study was only 4% [28]).

• Improvements in the control group as a result of participation in a research study have been anticipated [25].

• Design effects are calculated using intracluster correlation coefficients from data from similar populations in Galway and Scotland ([name], personal communication).

A total sample size of 907 patients recruited from 46 practices gives a varying but minimum power of 80% to detect significant changes in proportions with poor blood pressure and cholesterol control, physical and mental well being (SF-12) and hospital readmissions at two years. (Detailed power calculations are given below). This allows for a final patient follow-up and retention rate of 70% and a practice attrition rate of 10%. The number of practices is rounded up from 46 to 48, to allow equal numbers of practices to be recruited in each of the three study centres. Sixteen practices will therefore be recruited in each of the three centres, eight intervention practices and eight control practices. Twenty patients are recruited in each practice. Final data analysis will incorporate modelling techniques that are more statistically efficient and will ensure greater power to detect significant changes in study outcomes.

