## Power Calculations – Further Detail

### Blood pressure

44% of Irish patients with established heart disease have a systolic blood pressure above recommended guidelines (SBP >140 mmHg) ([name], personal communication). Previous research indicates that an improvement of 20% can be anticipated in the control group [10]. Taking this into consideration, a sample size of 408 gives 80% power to detect a 50% reduction in the proportion of patients with a SBP above 140 mmHg (i.e. giving a proportion of 22%) in the intervention group with a corresponding 20% improvement in the control group. Other studies have indicated that it is possible to achieve similar targets in general practice populations with established coronary heart disease [15]. To take account of cluster randomisation, based on recruiting 15 patients per cluster, a design effect size of 1.15 and an intracluster correlation coefficient of 0.011 [4,10] suggests a sample size of 470 patients from 31 practices. Allowing for a final response rate of 70% and a practice attrition rate of 10% requires recruitment of 670 patients from 34 practices.

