### Cholesterol

36% of Irish patients have a baseline cholesterol level above the upper recommended limit, i.e. greater than 5 mmol/l ([name], personal communication). To demonstrate an improvement of 50% in the intervention group and 20% in the control group requires a sample size of 500 patients. To ensure a final sample of 15 patients per practice, this is inflated by a design effect size of 1.27 (ICC = 0.019; [name], personal communication) to give a sample of 635 patients from 42 practices. This is increased to 907 patients from 46 practices to allow for final follow up and response rate of 70% and practice attrition of 10%.

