### Aim

The aim of the economic analysis is to provide both cost minimization analysis and cost-effectiveness analysis of secondary prevention of heart disease in general practice. The cost effectiveness analysis provides information on the marginal costs and effects of the intervention relative to the alternative through the calculation of an incremental cost-effectiveness ratio. In situations where there is no significant difference in effects, the use of cost minimization analysis allows the reporting of cost differences only.

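### One patient-cost item is defined by attribution to the intervention, so it cannot mean the same in both arms or reliably give the between-arm cost difference

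*Protocol article*

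**What the plan says.** All references are to the Protocol article.

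- **Economic Evaluation, Data Collection**, lists four kinds of data for patient costs. Three do not depend on arm: occupation, travel and waiting for practice and hospital visits, and GMS status. The fourth is "Patient-estimated additional expenditure or savings made in the process of lifestyle change as a result of the intervention", with shopping bills, exercise facilities and giving up smoking as examples.
- **Economic Evaluation, Introduction**, sets a wide scope: "The patient and family costs include any out-of-pocket expenses and any own time input into the treatment process". It makes cost-effectiveness analysis the main method, with effects drawn from the primary and secondary outcomes.
- **Economic Evaluation, Aim**, fixes the target as "marginal costs and effects of the intervention relative to the alternative through the calculation of an incremental cost-effectiveness ratio".
- **Control Practices** says: "Data are collected for patients in intervention and control practices in identical ways". Control patients otherwise continue with usual care.
- **Sample Size Calculation** says: "Improvements in the control group as a result of participation in a research study have been anticipated". The power calculations put this at 20% for blood pressure ("Previous research indicates that an improvement of 20% can be anticipated in the control group") and use the same 20% for cholesterol and re-admissions.

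**The concern.** An incremental cost needs the same quantity measured in each arm. Here the quantity is tied by definition to one arm. A control patient who pays for a gym or saves by giving up cigarettes has no intervention to attribute it to. An intervention patient who does the same must decide how much would have happened anyway. Intervention patients know they are in a programme: they set a lifestyle priority with their practitioner and are given a booklet on smoking, exercise and healthy eating. They have no means of separating the effect of that programme from the effect of being in a study, which the protocol itself expects to be present.

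At stake is the consistency of the cost-effectiveness ratio. Exercise, diet and smoking are secondary outcomes and so may serve as effect measures. The effect would then be a randomised difference between arms, while the money spent or saved on those same changes would rest on patients' own attribution.

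**Working it through.** The protocol gives no monetary figure for lifestyle spending, so there is no stated result to reproduce. The check sets the texts side by side and adds a short algebraic illustration.

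**Texts.**
1. The Aim requires cost in the intervention arm minus cost in the control arm. Both terms must be the same measure.
2. The item measures change attributed to the intervention. In the control arm that is undefined, or nil if taken literally.
3. Control Practices requires collection to be alike in both arms. Putting the same words to both arms would meet this in form, but the answers would not mean the same thing.
4. Sample Size Calculation expects some improvement among controls, so a nil change in lifestyle spending there cannot simply be presumed.

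Statements 1 to 3 cannot all be met with the present wording, and statement 4 gives a reason why it may matter.

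**Illustration (assumed quantities only).** Let the mean change in lifestyle spending be C in the intervention arm and r × C in the control arm. The true increment is C(1 − r). Let intervention patients report a share a of C, and let controls report b × C. The recorded increment is C(a − b), and

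recorded / true = (a − b) / (1 − r).

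- *Intervention patients report their whole change, controls report nothing* (a = 1, b = 0). The ratio is 1/(1 − r): 1.00 at r = 0, 1.11 at r = 0.1, 1.25 at r = 0.2, 1.67 at r = 0.4, 2.50 at r = 0.6.
- *Intervention patients attribute perfectly, controls report nothing* (a = 1 − r, b = 0). The ratio is 1.00 for any r below 1. The item is then already an increment and there is no error.
- *Intervention patients attribute perfectly, controls report their whole change* (a = 1 − r, b = r). The ratio is (1 − 2r)/(1 − r): at r = 0.2, 0.6/0.8 = 0.75; at r = 0.4, 0.2/0.6 = 0.33. The control change is subtracted twice.

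The same wording can therefore overstate the component, understate it or leave it right, depending on how patients in each arm read the question. Because C may be a net cost or a net saving, the effect on total cost can also go either way.

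The value r = 0.4 is 20%/50%, from the planning assumptions (for cholesterol, "To demonstrate an improvement of 50% in the intervention group and 20% in the control group requires a sample size of 500 patients"). Those percentages are relative reductions in the proportions with raised systolic pressure, raised cholesterol or a hospital admission. Nothing in the protocol says that lifestyle spending moves with them, so 1.67 is no estimate for this trial.

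**The case against.** The strongest reply has four parts.

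**The form is not shown.** The article gives a one-line description. The main questionnaire is in an appendix that is not at hand, and the Data Collection section for the trial lists only journey times under its economic questions. The qualitative section mentions a patient questionnaire within the economic evaluation. The actual question may be neutral and may go to both arms. This stands as a limit on what can be concluded, but the article's definition is what it fixes, and that definition is arm-dependent.

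**Data are collected alike in both arms.** A reader might infer that control patients are entered as zero and that the incremental patient cost is therefore overstated, perhaps about 1.7-fold. The protocol does not support this. Nowhere does it withhold the item from controls or set them to zero, and its rule on identical collection points the other way. That rule does not cure the wording, though: it makes the two statements hard to reconcile.

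**An attributed change is already an increment.** Taken literally this is right, and a nil value for controls would then be consistent with the target. It depends on patients knowing what they would have done without the programme, which cannot be verified when they know they are receiving it.

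**The stakes are small.** Blood pressure and cholesterol can improve through prescribing with no lifestyle spending, the protocol describes smoking as already low in this population, and the item is one part of patient cost. All of this stands and limits the weight of the point.

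**Conclusion.** The point holds as a fault in definition. The item is worded so that it cannot carry the same meaning in both arms, it conflicts with the protocol's own rule on data collection, and it cannot reliably give the between-arm difference that the economic aim requires.

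Neither a size nor a direction of bias is shown. The ratios in the illustration rest on assumed values of r, a and b, and there is no error at all if controls do not change their spending and intervention patients attribute all of theirs. The effect is confined to one component of patient cost, whose share of total cost the protocol does not give. Health-service use, prescriptions, travel, capital and intervention costs are unaffected, as are the clinical primary outcomes. The correction is still worth making, because a comparable control-arm answer would be hard to recover reliably once follow-up has ended.

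**What to change.** In Economic Evaluation, Data Collection, delete the attribution to the intervention. Ask every patient in both arms, at one and two years and over the same recall period, one neutral question about change in spending or savings on diet, exercise and smoking, with no mention of the programme. State that the incremental patient cost for this component is the difference between arms. This brings the item into line with Control Practices and with the economic Aim.

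A question about change is enough. Asking for total spending on food, tobacco and exercise would add noise without need.

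The cost is one more item for control patients and somewhat more variance than self-attributed change would give. In return, the comparison rests on randomisation and not on patients' own judgement of cause.
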